## 13 Time and Events Table

All baseline investigations should be performed prior to the start of the chemotherapy. Hematological and biochemical investigations should be obtained within one week of start of chemotherapy. Imaging investigations may be performed within 2 weeks of the start of chemotherapy. All investigations indicated on the chart below will be repeated on the day of the chemotherapy prior to the administration of the chemotherapy.

| Day                                                       | Pre-study | C1D1 | C1D8 | D1 of first 3 cycles | D1 of subsequent cycles | Progression |
|-----------------------------------------------------------|-----------|------|------|----------------------|-------------------------|-------------|
| Eligibility Screen                                        | ✓         | -    | -    | -                    | -                       | -           |
| Informed Consent                                          | ✓         | -    | -    | -                    | -                       | -           |
| Multi speciality Board                                    | ✓         | -    | -    | -                    | -                       | -           |
| History                                                   | ✓         | -    | ✓    | ✓                    | ✓                       | ✓           |
| Physical Examination                                      | ✓         | -    | ✓    | ✓                    | ✓                       | ✓           |
| Toxicity Charting                                         | -         | -    | ✓    | ✓                    | ✓                       | ✓           |
| Complete Hemogram                                         | ✓         | -    | ✓    | ✓                    | ✓                       | ✓           |
| Renal Function                                            | ✓         | -    | ✓    | ✓                    | ✓                       | ✓           |
| Liver Function                                            | ✓         | -    | ✓    | ✓                    | ✓                       | ✓           |
| Serum Electrolytes (Ca 2+ / Mg 2+ ) | ✓         | -    | ✓    | -                    | -                       | -           |
| Biopsy                                                    | ✓         | -    | ✓    | -                    | -                       | ✓           |
| Serum markers ( ELISA +                                   | ✓         | -    | ✓    | ✓                    | -                       | ✓           |

|                  |   |   |   |   |   |   |
|------------------|---|---|---|---|---|---|
| Flow)            |   |   |   |   |   |   |
| MRI/CT Head Neck | ✓ | - | - | ✓ | ✓ | ✓ |
| MCT Chemotherapy | - | ✓ | ✓ | ✓ | ✓ | - |

Table 7 : Study calendar

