### 7.2 Secondary objective ( both stages)

1. To find out the frequency of maximum grade of toxicity (hematological and non hematological) in accordance with CTCAE (common terminology criteria for adverse events, NCI,USA) version 4.03 with the combination metronomic therapy
2. To study the evolution in serum and tissue biomarker levels during metronomic chemotherapy and their relationship to disease control
  - a. Serum angiogenic biomarkers : VEGF, VEGFR1-3, Tie-2, Angiopoietin 1-2, Thrombospondin 1, Vaso-inhibin, Angiostatin, Endostatin ,IL-8, Circulating endothelial cells and Endothelial progenitor cells,CAIX,osteopontin,
  - b. Tumor tissue marker : Thymidine phosphorylase, Hypoxia inducible factor I-alpha, DLL, SPARC , FOX-p3 Treg
3. To develop Pharmacokinetics-Pharmacodynamics (PK-PD) Model of methotrexate using CECs and serum angiogenic biomarkers as PD endpoints

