### **Followup**

Patients will receive MCT at 4 weekly intervals continuously till progression or intolerable side

As this is a stage I/II trial hence further followup after treatment progression will be conducted as per institutional norms.

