### 11.4 Toxicities and Dosing Delays / Dose Modifications

All patients will be evaluable for adverse events due to chemotherapy during the study. The schedule for monitoring of adverse events is mentioned under the time and events table. All toxicities will be evaluated as per the NCI CTCAE 4.03 criteria. The final dose modification according to the following tables should be based upon the worst grade of adverse event experienced. If any of the treatment agents is held or discontinued for toxicity or intolerance, further protocol directed treatment will be stopped. Held doses of any agent will not be made up at a later date. If more than one dose reduction applies, then use the most stringent (i.e., the greatest dose reduction). Doses that are reduced at any point during a cycle will not be re-escalated. Grade I toxicities will not result in dose modifications. Patients will be removed from the protocol in the event of discontinuation of any of the agents mentioned in the protocol as per criteria mentioned below.

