**Non Hematological Toxicity**

MCT has very limited non hematological side effects. The subsequent subsections show the dose modifications that should be done for derangements of metabolic parameters and non hematological toxicity during the treatment.

Nausea & Vomiting

Nausea and vomiting are unlikely. Primary prophylaxis against nausea and vomiting is not required as per the schedule mentioned in Treatment schedule above. Patients with Grade III – IV nausea and vomiting should have the dose withheld till the nausea, vomiting subsides to Grade I or less. Patients who have had one episode of Grade III / IV nausea or vomiting should have primary prophylaxis with addition of ondansetron (4 mg BD ) from the subsequent cycles of methotrexate chemotherapy. If patients continue to have Grade III- IV vomiting despite instituting antiemetic ondansetron then from the subsequent cycles of methotrexate chemotherapy additive antiemetics can be added. If in spite of high risk antiemetic prophylaxis patients continue to have vomiting ( Grade III-IV) then methotrexate should be discontinued.

Nephrotoxicity

Nephrotoxicity will be monitored in accordance with following time points

Cycle 1: Renal function test ( inclusive of serum urea, creatinine ,Na and K) for monitoring of toxicity will be done on D8 ( D7-D10)

Subsequent Cycles : Renal function test ( inclusive of serum urea, creatinine ,Na and K) for monitoring of toxicity will be done at start of each cycle.

The dose reduction in case of nephrotoxicity will be done in accordance with below mentioned table.

| Serum creatinine clearance | Methotrexate | Celecoxib  | Erlotinib          |
|----------------------------|--------------|------------|--------------------|
| > 30 ml/min                | 100 % dose   | 100 % dose | No dose adjustment |
| 15-30 ml/min               | 50% dose     | Avoid      | No dose adjustment |
| < 15 ml/min                | Avoid        | Avoid      | No dose adjustment |

Table 5: Dose reductions in case of nephrotoxicity

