### Hepatic Dysfunction

Patients should be monitored for liver dysfunction prior to each chemotherapy cycle. Dose modifications will be made as per the following table.

| Bilirubin |        | ALT/AST  | Methotrexate | Celecoxib | Erlotinib |
|-----------|--------|----------|--------------|-----------|-----------|
| 2-4 x ULN | And/or | >4 x ULN | 75% dose     | 50 % dose | 50 % dose |
| >4 x ULN  | And/or | >4 x ULN | Avoid        | Avoid     | Avoid     |

Table 6: Dose adjustments to be made as per hepatic function.

The above biochemical parameters except Creatinine Clearance will be monitored prior to each cycle. Patients will have creatinine clearance measured prior to each cycle in case of any episode of Grade II renal toxicity prior to each cycle of chemotherapy.

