## **21 Harms**

An adverse event will be defined as any untoward medical occurrence in a subject without regard to the possibility of a causal relationship. Adverse events will be collected after the subject has provided consent and enrolled in the study. If a subject experiences an adverse event after the informed consent document is signed (entry) but the subject has not started to receive study intervention, the event will be reported as not related to study drug. All adverse events occurring after entry into the study and until hospital discharge will be recorded. An adverse event that meets the criteria for a serious adverse event (SAE) between study enrollment and hospital discharge will be reported to the local IRB [institutional review board] as an SAE.

If chemotherapy is discontinued as a result of SAE, study personnel will document the circumstances and data leading to discontinuation of treatment. A serious adverse event for this study is any untoward medical occurrence that is believed by the investigators to be causally related to study-drug and results in any of the following: Life-threatening condition (that is, immediate risk of death); severe or permanent disability, prolonged hospitalization, or a significant hazard as determined by the data safety monitoring board. Serious adverse events occurring after a subject is discontinued from the study will NOT be reported unless the investigators feels that the event may have been caused by the study drug or a protocol procedure. Investigators will determine relatedness of an event to study drug based on a temporal relationship to the study drug, as well as whether the event is unexpected or unexplained given the subject's clinical course, previous medical conditions, and concomitant medications.

The study will monitor the following adverse events during chemotherapy cycles:

Haematological

Anemia

Leucopenia

Thrombocytopenia

Febrile neutropenia

Non hematological

Nausea

Vomiting

Oral mucositis

Pain

Xerostomia

Dysphagia

Dyspnea

Anorexia

Diarrhea

Constipation

Dysgeusia

Fatigue

Peripheral Sensory neuropathy

Peripheral Motor Neuropathy

Nail infection

Weight loss

Myalgia

Joint Pain

Alopecia

Biochemical

Increase in serum creatinine

Increase in Alanine Aminotransferase (SGPT)

Increase in Alkaline Phosphatase (ALP)

Increase in Bilirubin

Decrease in serum albumin (Hypoalbuminemia)

Increase or decrease in Serum electrolytes

Sodium

Potassium

Corrected Calcium

Magnesium

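### Table 7 schedules calcium and magnesium only to cycle 1 day 8, while Section 21 lists both as adverse events monitored during the chemotherapy cycles; the passages need reconciling (minor)

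*Protocol*

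**What the plan says.** **Schedule.** In Table 7 (Section 13), the row "Serum Electrolytes (Ca 2+ / Mg 2"+) has ticks at pre-study and C1D8. It has dashes at C1D1, D1 of the first 3 cycles, D1 of subsequent cycles and progression. Toxicity charting, hemogram, renal function and liver function are ticked in all of the later columns. A sentence above the table says that the charted investigations are repeated on chemotherapy days before dosing. Section 11.4 refers the reader to this table for the timing of adverse-event monitoring.

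**Events to be monitored.** Section 21 states "The study will monitor the following adverse events during chemotherapy cycles". Under its biochemical group it lists "Increase or decrease in Serum electrolytes", naming sodium, potassium, corrected calcium and magnesium.

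**Objective.** The first secondary objective, for both stages, is "To find out the frequency of maximum grade of toxicity (hematological and non hematological) in accordance with CTCAE". Section 11.4 adds that dose modification "should be based upon the worst grade of adverse event experienced".

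**Duration.** The Followup section says "Patients will receive MCT at 4 weekly intervals continuously till progression or intolerable side" (the sentence breaks off there).

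**Other per-cycle chemistry.** Under nephrotoxicity in Section 11.4: "Renal function test ( inclusive of serum urea, creatinine ,Na and K) for monitoring of toxicity will be done at start of each cycle". Under hepatic dysfunction: "The above biochemical parameters except Creatinine Clearance will be monitored prior to each cycle".

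**The concern.** Section 21 treats the four electrolytes alike and sets no limit to cycle 1. The calendar does not treat them alike: sodium and potassium come with the renal panel at every cycle start, whereas calcium and magnesium have no scheduled value after C1D8. A maximum grade depends on how long and how often one looks. If a frequency of maximum Ca/Mg grade is tabulated beside the other laboratory toxicities, it will rest on one scheduled on-treatment sample, while its neighbours rest on sampling up to progression. A reader of that table could not tell a low rate from a short look. No analysis plan can recover tests that were never scheduled, so the matter belongs in the protocol.

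**Working it through.** The plan gives no figure on this point, so there is nothing to reproduce. The check has two parts.

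**1. Is Ca/Mg scheduled anywhere else after C1D8?**

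- Table 7: no; all later columns are dashed.
- Section 11.4, nephrotoxicity: the per-cycle panel is urea, creatinine, Na and K. Ca and Mg are not in it.
- Section 11.4, hepatic dysfunction: the parameters it refers back to are bilirubin, ALT/AST and renal function. Ca and Mg are not among them.
- Sentence above Table 7: on its broadest reading it would repeat Ca/Mg on chemotherapy days. The same reading would also repeat eligibility screening, consent and biopsy, and would empty every dash of meaning. The narrower reading, that tests are repeated where ticked, fits the table. The text does not settle it.

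So there is one scheduled on-treatment value per patient. Methotrexate is given on D1, D8, D15 and D22. A C1D8 sample drawn before that day's dose therefore follows a single methotrexate dose.

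**2. How much of the treatment period does that value cover?** (illustration)

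Assumption: time on treatment is exponential with median m days, so λ = ln 2 / m.

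- Share of patient-time in the first 8 days = 1 − exp(−8λ).
- Expected cycle-start visits from cycle 2 on = Σ over k ≥ 1 of exp(−28λk) = 1 / (exp(28λ) − 1).

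Medians: 60 and 90 days are assumed. The 148 days is the median PFS of the earlier small MCT-E study in Section 4.4, used here as a stand-in for time on treatment.

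| Median (days) | Share in first 8 days | Later cycle-start visits, mean |
|---|---|---|
| 60 | 1 − exp(−0.0924) = 8.8% | 2.6 |
| 90 | 1 − exp(−0.0616) = 6.0% | 4.2 |
| 148 | 1 − exp(−0.0375) = 3.7% | 7.1 |

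Cross-check with Section 15, which assumes exponential PFS with 3-month rates of 0.50 (H0) and 0.60 (H1), taking treatment to last until progression. The medians are 91.3 and 123.9 days. C1D8 falls 7 days after the first dose, or up to 9 days if the D7-D10 window given for the hemogram and renal tests applies.

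| | Share to day of draw (7 to 9 days) | Later cycle-start visits, mean |
|---|---|---|
| H0 | 5.2% to 6.6% | 4.2 |
| H1 | 3.8% to 4.9% | 5.9 |

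Both routes put coverage at roughly 4-9% of on-drug time. They also show some 3 to 7 later visits per patient at which blood is taken for renal and liver tests but no Ca/Mg result is scheduled.

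**The case against.** **What stands.** Monitoring during chemotherapy cycles sets no frequency, and C1D8 lies within a cycle, so a baseline plus an early check is not a strict contradiction of Section 21. The sentence above Table 7 leaves room for a fuller schedule. Section 21 puts Ca/Mg in a biochemical group, while the secondary objective speaks of hematological and non-hematological toxicity, so their inclusion is plausible but not spelled out. Nothing in dose selection, sample size, PFS or the dose-modification tables uses Ca or Mg.

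**Stronger readings that the documents do not support.**

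- A reader might infer that all ascertainment ends at day 8, or that the maximum grade must be the day-8 grade. It need not be. Toxicity charting continues at each cycle start and at progression, and a clinically prompted test could be recorded there. Only scheduled, systematic detection is limited.
- A reader might infer that 91-96% of Ca/Mg events would be missed. Patient-time is not event count. The protocol gives no Ca/Mg event rate and no time pattern, so there is no basis for saying that such events build up on drug.
- A reader might infer that the rates will be presented as whole-treatment rates. The protocol does not say how they will be tabulated.
- A reader might take the hypercalcemia exclusion as evidence of on-drug risk. It applies at presentation only.

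**What does not answer the point.** If the broad reading of the sentence above the table was intended, the dashes are wrong and still need correcting.

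**Conclusion.** The mismatch is real and minor. As Table 7 stands, systematic detection of calcium and magnesium toxicity rests on one on-treatment value at about day 8. Treatment continues to progression, and Section 21 sets no such limit. The maximum-grade frequencies for these two items would not describe the whole treatment period.

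The 4-9% coverage depends on the exponential assumption and on medians of 60 to 148 days, of which only the last comes from the protocol, and as a PFS. Sections 11.3 and 11.4 can end treatment before progression, so time on drug may be shorter than PFS, which would raise the share covered. The figure describes coverage and says nothing about how many events are missed.

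The effect is confined to two laboratory items within one secondary safety objective.

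**What to change.** Reconcile Table 7, the sentence above it and Section 21. Either of two changes would do, and the choice is the sponsor's.

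- Align the Ca/Mg row with the renal and liver rows, using blood already drawn at those visits. Cost: two extra analytes per visit.
- Or state in Section 21 that calcium and magnesium toxicity is ascertained systematically only to C1D8, and report the two items under that label, with any later clinically prompted findings shown separately. Cost: wording only, at the price of having no whole-treatment rate for these items.

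In either case, reword the sentence above Table 7 so that it cannot be read against the dashes, for example by limiting it to the visits ticked for each test.

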## 14 Study timeline

| Work                                                                                                                                                                                   | 1st year                              | 2nd year | 3rd year                                                   | 4th year | 5th year |
|----------------------------------------------------------------------------------------------------------------------------------------------------------------------------------------|---------------------------------------|----------|------------------------------------------------------------|----------|----------|
| Clinical work : Consent, patient selection, drug administration, clinical and radiological monitoring for clinical benefit rate, progression and toxicity. Duration : 4.3 years |                                       |          | 3 month block for selection of metronomic dose for stage 2 |          |          |
|                                                                                                                                                                                        | Stage 1                               |          | ↕                                                          | Stage 2  |          |
| Flow cytometry :Endothelial cell suppression ,Duration :4.3 years                                                                                                               | Will be done during Stage 1 & Stage 2 |          |                                                            |          |          |
| Sample collection : Blood sample and tissue collection for biomarkers,Duration;4.3 years                                                                                        | Will be done during Stage 1 & Stage 2 |          |                                                            |          |          |
| ELISA ( done post completion of stage 1 & 2 clinical work, Time duration = 6 months)                                                                                            |                                       |          |                                                            |          |          |
| IHC & Microarray ( done post completion of stage 1 & 2 clinical work, Time duration = 6 months)                                                                             |                                       |          |                                                            |          |          |
| Analysis & scientific draft ( Duration=3 months)                                                                                                                            |                                       |          |                                                            |          |          |

## 15 Sample size calculation

**Total sample size** : Stage 1 ( 20-30 patients) + Stage 2 ( 76 patients). In stage the continuous reassessment model will be used hence the sample size would be maximum of 30 and minimum around 20. The exact calculations done in both stages are described below in details.

Stage 1 : Flexible-finite sample based approach will be adopted to select the circulating endothelial cells (CEC) interval boundaries and further to use optimum interval design. During the trial, we will continuously update the posterior estimates of decline in CEC and clinical benefit rate and assign patients to the most appropriate dose combination (Figure 1). The Bayesian adaptive screening design will be used to simultaneously select among possible treatment dose combinations. The design is based on formulating the selection procedure as a Bayesian hypothesis testing problem in which the superiority of each treatment combination is equated to a single hypothesis. During the trial conduct, we intend to use the current values of the posterior probabilities of all hypotheses to adaptively allocate patients to treatment combinations. The dose-finding decision will be decided on the twin endpoints the clinical benefit rate at 2 months and proportional decline in CEC at D8 of first cycle. Figure 2 will be used for decision making.

Stage 2: It was assumed that the 3-month progression-free survival (PFS) rate of a standard cancer therapy is 0.50 (H0). An improvement to 0.60 would be considered clinically significant (H1). Assume both the null and alternative PFS distributions follow an exponential distribution. The 1-sided type I error rate of 0.05 and type II error rate of 0.1. Prior assumption includes a fixed enrollment rate of 3 patients per month. We require a stop of 3 months at the end of Stage 1. The library("OptInterim") has been used to calculate the sample size. A 20%extra patient would be taken to account for lost to follow up data. Hence **a total of 76 ( 63 patients +13 patient) sample size is found suitable to carry out the study for stage II with single arm drug therapy.**

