## 6 Hypothesis

**Stage 1: Whether a lower dose of methotrexate is clinically and biologically more effective than 15 mg /m^2 weekly dose?** *The dose of methotrexate associated with maximum CBR at 2 months and/or decline in CEC at D7 of first cycle would be selected .*

**Stage 2 : Whether MCT-E combination of celecoxib, erlotinib and methotrexate (in OBD) would lead to a median PFS of > 3 months in platinum insensitive oral cancers?**

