## **25 Feasibility**

On an average in TMC, 30 chemoresistant patients receive palliative chemotherapy for advanced oral cavity cancers per month. The maximum required sample size for the present study is 30 patients ( 6 x 5 dose levels). Assuming that only 10% of the eligible patients are willing to participate in this trial we expect 30 patients to be recruited within a period of 24 months from the date of start of recruitment. Hence around 70 patients ( cumulative number required for stage I/II ) would be recruited within 4 years.

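### Stage 2's 63 (76 with allowance) patients do not give the stated 90% power for 3-month PFS of 0.50 versus 0.60 under any standard one-sample test

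*Protocol*

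**What the plan says.** Section 15 sets the Stage 2 null as follows: "It was assumed that the 3-month progression-free survival (PFS) rate of a standard cancer therapy is 0.50 (H0"). The alternative is "An improvement to 0.60 would be considered clinically significant (H1"). The distribution is fixed: "Assume both the null and alternative PFS distributions follow an exponential distribution". The error rates are "The 1-sided type I error rate of 0.05 and type II error rate of 0.1", that is, 90% power. Accrual is stated too: "Prior assumption includes a fixed enrollment rate of 3 patients per month". The R library OptInterim is cited, without its options or a decision rule. The result is that a "total of 76 ( 63 patients +13 patient) sample size is found suitable", where the 13 are a 20% addition for loss to follow-up.

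Section 6 asks whether the regimen "would lead to a median PFS of > 3 months in platinum insensitive oral cancers". Section 16.1 says that median PFS will be estimated by Kaplan-Meier and names no test.

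On accrual, Section 15 totals 20-30 patients in Stage 1 plus 76 in Stage 2. Section 25 says: "Hence around 70 patients ( cumulative number required for stage I/II ) would be recruited within 4 years".

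**The concern.** The target is a 10-point gain in a 3-month rate, from 0.50 to 0.60. That is a modest effect for a single-arm study of 63 patients, and 90% power at one-sided 0.05 would normally need either far more patients or far more events than 63.

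If the stated type II error is wrong, anyone relying on Section 15 believes that the chance of missing the target effect is 10% when it is materially larger. The concept sheet treats a median PFS above 3 months as opening a new treatment option, so the reverse matters as well: an inconclusive Stage 2 could be read as evidence against the regimen when the study was never likely enough to detect the effect it was sized for.

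**Working it through.** **Inputs (all from Section 15).** 3-month PFS 0.50 under H0 and 0.60 under H1; exponential PFS; one-sided alpha 0.05 (z = 1.645); type II error 0.10 (z = 1.282); 3 patients per month; 63 patients, or 76 with the addition.

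**Can 63 be reproduced?** The 76 can: 63 × 1.2 = 75.6. The 63 cannot, by any of the methods below.

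**A. One-sample exponential or log-rank test, using all follow-up**
- Hazard ratio = ln 0.60 / ln 0.50 = 0.737, and ln(0.737) = −0.305. The median is 3 months under H0 and 3/0.737 = 4.07 months under H1.
- Events for 90% power = (1.645 + 1.282)² / 0.305² = 91.9, about 92. A score-type approximation gives about 80. Both exceed 63 and 76.
- Power with d events = Φ(√d × 0.305 − 1.645).

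| Situation | Events | Power |
|---|---|---|
| All 63 progress | 63 | 78% (exact gamma test 79%) |
| n = 63, simulated, 24 months after last patient | about 63 | 77% |
| n = 63, simulated, 3 months after last patient | about 53 | 72% (formula at 52 events: 71%) |
| All 76 progress, none lost | 76 | 85% |
| n = 76, no loss, simulated, 24 months after last patient | about 76 | 83% |
| n = 76, no loss, simulated, 3 months after last patient | about 66 | 79.5% |

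The simulations use 3 patients per month. If the analysis took place as soon as accrual ended, power would be lower: 66% for 63 and 75% for 76.

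**B. Test of the 3-month rate**
- Exact binomial, n = 63: success at 39 or more, actual alpha 0.038, power 43%. For n = 76: success at 46 or more, alpha 0.042, power 51%.
- Normal approximation: Φ[(0.10 − 1.645 × 0.5/√n) / √(0.24/n)] = 48% at 63 and 54% at 76.
- Complementary log-log (log cumulative hazard), n = 63: the standard error is √(0.4/(0.6 × 63))/0.511 = 0.201 under H1 and √(1/63)/0.693 = 0.182 under H0. Power is Φ(0.305/0.201 − 1.645) = 45% with the H1 error throughout, and Φ[(0.305 − 1.645 × 0.182)/0.201] = 51% with the H0 error for the critical value. At n = 76 the two versions give 51% and 57%.
- Patients needed for 90% power: 210-211 (normal: (1.645 × 0.5 + 1.282 × √0.24)²/0.10² = 210.3), 213-224 (exact, because of its saw-tooth), 218 (Nelson-Aalen), 210-235 (log cumulative hazard).

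**C. Alternative for which 90% holds at 63**
- Exponential/log-rank, 63 events: ln HR = −(1.645 + 1.282)/√63 = −0.369, HR = 0.692, and 0.50^0.692 = 0.62.
- 3-month rate, exact test with 39 of 63: power is 88% at 0.68 and 91% at 0.69, so about 0.69.

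**D. Accrual figures**
- Section 15: 20 + 76 = 96 to 30 + 76 = 106 patients. Section 25: around 70.
- Section 25: 30 patients in 24 months = 1.25 per month. Section 15: 3 per month. Section 25's own premise, 10% of 30 eligible patients a month, is also 3 per month and does not lead to 30 in 24 months.

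**The case against.** The strongest reply is that the protocol names a software package but no test, boundary or options, and that an analysis plan not shown may supply them. This stands in part: the shortfall cannot be fixed at one number, and OptInterim itself was not run. It does not rescue the stated power. The hypotheses, alpha, type II error and distribution are all written in Section 15, the more efficient class of test already needs more events than there are patients, and an interim futility look would raise the required number rather than lower it.

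It is also fair to say that the loss is moderate under the favourable reading. If all 76 are followed on an exponential/log-rank test, the risk of missing the effect is about 15-21%. A reader who takes only the 63-patient figures would put the risk at 22-57% and overstate the case.

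Two stronger readings are tempting and should not be drawn.
- A reader might infer that the 20% allowance was added the wrong way, because 63/0.8 = 79. Section 15 says only that 20% extra will be taken, which is what 76 is. It does not claim that 63 remain after a 20% loss, and patients lost to follow-up are censored in a Kaplan-Meier analysis and still contribute time.
- A reader might infer a false-positive rate of about 50%, because a median of 3 months is exactly the null and a point estimate exceeds it half the time. No section declares success on a point estimate. Section 6 poses a question, Section 16.1 describes estimation, and a decision rule is commonly left to the analysis plan.

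**Conclusion.** The stated type II error of 0.1 is wrong for the stated inputs. Power is about 71-78% (63 patients) or 79-85% (76, no loss) with an exponential/log-rank test, and about 43-51% or 51-57% with a test of the 3-month rate. The exponential figures assume the constant hazard that Section 15 itself assumes; their lower ends assume an analysis about 3 months after the last patient, and their upper ends that every patient progresses. Because H0 and H1 are written as 3-month rates, the lower figures fit the hypotheses as worded. Because PFS is assumed exponential and the objective is a median, the higher ones are also arguable. Neither reaches 90%.

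Where 63 came from is not stated and cannot be recovered from the document. The conflict between around 70 and 96-106 patients, and between 1.25 and 3 patients per month, is a separate inconsistency that does not bear on the power result.

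**What to change.** 1. In Section 15, keep 76, name one primary Stage 2 test, and do one of two things. Either replace the type II error of 0.1 with the power the design has under that test (about 71-78% at 63 and 79-85% at 76 for exponential/log-rank; about 43-51% and 51-57% for the 3-month rate), or restate the alternative for which 90% holds at 63 (about 0.62 with 63 events, or about 0.69 for the 3-month rate).
2. If the exponential/log-rank test is chosen, base the success criterion on it: the one-sided 95% lower limit for the median, from the same model, lies above 3 months. Do not pair it with a Kaplan-Meier limit at 3 months, which is a landmark test with the lower power. Align Sections 6 and 16.1 with this.
3. Separately, reconcile the total in Section 25 with the 96-106 in Section 15, and its implied 1.25 patients per month with the assumed 3.

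The cost is wording in Sections 6, 15, 16.1 and 25 and a less favourable power or target effect on paper. No patients are added. Keeping both 0.60 and 90% power would instead require a larger Stage 2: enough patients for about 92 events, or about 210-235 patients for a 3-month rate.
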